### Intervention

*Control group*: Participants in the control arm will undergo *Standard Consent (SC)* which will consist of paper PIL provided by EIDO™ healthcare followed by a verbal discussion (standardised by following a checklist of topics to discuss) with the responsible consultant surgeon and signing of their consent form. The time taken to read the PIL (recorded with a stopwatch) will be recorded. The time spent with the responsible surgeon will also be recorded, as will the number of questions asked by the patient.*Intervention*: Participants randomised to the intervention dHET will receive the dHET followed by a verbal discussion (as above) and signing of their consent form. The dHET will be delivered on a tablet computer and facilitated by a research assistant who will ensure all technological issues are overcome but will not engage with the participant with regard facilitating better understanding of the content. The digital offering will be interactive; patients will be able to traverse through each section at their own pace with the ability to re-visit sections as many times as they wish. It also contains a short narrated animation of the procedure, which they can play, rewind or fast forward. The time spent reading each section of the dHET and time spent watching the animation will be recorded. The time spent with the responsible surgeon will also be recorded, as will the number of questions asked by the patient.

All patients will complete a knowledge questionnaire at baseline, post intervention on the day of surgery and at the 2-week follow-up telephone interview. As no validated knowledge questionnaire for EVTA procedures was available, we developed one based on information provided in the EIDO^TM^ PIL and from a separate body of work by our team—expert consensus for essential information for varicose vein surgery—a modified Delphi study [27]. The knowledge questionnaire consists of 20 True or False questions. Patients are encouraged not to guess and to choose ‘Unsure’ if they do not know the answer. The questionnaire was piloted among post-operative EVTA patients and a mean score of 10.39 was achieved.

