### Data collection

Baseline patient demographic data will be collected pseudonymously from patients and/or from patient medical records. The following will be recorded:AgeGenderLevel of education (highest achieved)Primary schoolSecondary schoolThird levelHealth literacy—rapid estimate of adult literacy in medicine (revised) REALM-R—score of 6 or less considered to be at risk for poor health literacy [33, 34]

Outcome data will be collected prospectively. Outcome data and definitions are provided below:

Primary outcomes▪ Eligible participantsNumber of eligible participants (meeting inclusion criteria)▪ Recruitment numberNumber of participants consenting to participate▪ Retention rate(Number of patients who consent to participation) minus (number of patients who voluntarily withdraw) divided by (number of subjects who were randomised)• AcceptabilityMeasure of the perception among study personnel and patients that the dHET is agreeable or satisfactory. Measured on a 5-point Likert scale for study personnel (where 5 is highly acceptable and 1 is poorly acceptable) and using the post intervention CSQ-8 survey for patients.▪ Adherence to protocolNumber of patients who completed their assigned intervention, also includes the proportion of complete data for each outcome measure (CSQ-8, STAI-6, REALM-R, demographic data collection)▪ Barriers to assigned interventionNumber of patients not randomised due to staffing or time constraints (with reason recorded), technology issues with tablet/dHET/link to knowledge quiz/internet access• TimeTime (minutes) taken to complete the assigned intervention (and any delays caused as a result)

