### Sample size

As this is a pilot study, a formal sample size calculation was not performed [36]. Sample sizes of between 24 (12 per group) and 50 have been recommended variously for pilot studies [37–40]. Following these broad recommendations, we chose a recruitment sample size of 40 (20 per group) which would allow for a moderate dropout rate. A significant dropout rate (e.g. 40%) would reduce the pilot sample size to below a minimum 24, in which case a planned larger study would be called into question in the first place, having possible external validity issues, pragmatic or ethical concerns.

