## Trial progression

### Continuation criteria

Continuation criteria (Table 1) will be considered to determine whether further evaluation of this intervention is warranted (to test the effectiveness of the intervention) [41, 42]. These criteria are primarily based around the primary objective of feasibility and the potential for effectiveness and system-wide implementation.

**Table 1 Tab1:** Continuation criteria VVEIN pilot study

	**Proceed to RCT**	**Proceed to RCT following some changes to the protocol**	**Do not proceed to RCT unless problems can be overcome**
Recruitment	Recruitment of ≥ 80% study participants within 4 months	Recruitment of ≥ 60% study participants within 4 months [41]	Recruitment of < 60% study participants within 4 months
Retention	Retention of ≥ 80% of study participants for follow-up	Retention of ≥ 60% of study participants for follow-up	Retention of < 60% of study participants for follow-up
Feasibility and acceptability	dHET intervention on day ward acceptable to > 75% of study personnel (score of 4 or 5 on Likert scale) and patients involved (score of 28 or above on CSQ-8)	dHET intervention on day ward acceptable to > 50–74% of study personnel (score of 4 or 5 on Likert scale) and patients involved (score of 28 or above on CSQ-8)	dHET intervention on day ward acceptable to < 50% of study personnel (score of 4 or 5 on Likert scale) and patients involved (score of 28 or above on CSQ-8)
Non-adherence	Non-adherence to the intervention in < 10% (dHET and/or DOS questionnaires incomplete)	Non-adherence to the intervention in > 11–20% (dHET and/or DOS questionnaires incomplete)	Non-adherence to the intervention in > 21% (dHET and/or DOS questionnaires incomplete)

*dHET* Digital Health Education Tool, *DOS* Day of surgery

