### Follow-up

Participants shall be contacted by one researcher via telephone at two weeks for a virtual appointment and to complete the delayed knowledge recall questionnaire. Patients will also be followed up in a standardised fashion at 6 weeks in the vascular outpatient department at the study location or sooner should the need arise.

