## Discussion

The standard of care and ethical obligation of physicians’ is to ensure a patient is adequately informed prior to consenting to any invasive procedure. For many physicians working in a busy surgical practice such as vascular surgery, the process of informed consent has become increasingly difficult due to increased patients’ expectations and evolving technology within the speciality that can increase complexity of the procedures [21]. Several studies have shown benefit of digital tools, especially with active patient participation for improving patients’ understanding and satisfaction of informed consent [46, 47], but vascular surgery is underrepresented in these. In the context of a fast-paced surgical day ward where patient throughput is high and only minor delays in processes are accepted to ensure efficiency, this pilot study will support a decision to scale-up to a multicentre randomised controlled trial (RCT) if recruitment and retention is adequate.

The purpose of a future multi-centre RCT that could compare standard consent, which is the current practice, to a digital health education tool to assess the primary outcome measure of patients’ knowledge recall, would likely inform physician’s practices around informed consent and will be generalisable to other vascular and surgical procedures.

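### No progression criterion protects the 2-week knowledge score, and the completeness measure leaves the knowledge questionnaire off its list

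*Protocol article*

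**What the plan says.** All references are to the protocol article.

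- **Schedule (Intervention).** "All patients will complete a knowledge questionnaire at baseline, post intervention on the day of surgery and at the 2-week follow-up telephone interview". Under Follow-up, patients are reached "via telephone at two weeks for a virtual appointment and to complete the delayed knowledge recall questionnaire".
- **Role of the instrument.** Early and delayed knowledge recall are both secondary outcomes (Data collection). The Discussion describes a future multicentre trial "to assess the primary outcome measure of patients’ knowledge recall". It does not say at which time point.
- **Completeness (Data collection, Adherence to protocol).** The measure counts patients who completed their assigned intervention and "also includes the proportion of complete data for each outcome measure (CSQ-8, STAI-6, REALM-R, demographic data collection").
- **Non-adherence row (Table 1, Continuation criteria).** The *Proceed* column reads "Non-adherence to the intervention in < 10% (dHET and/or DOS questionnaires incomplete"). DOS stands for day of surgery.
- **Retention row (Table 1).** The *Proceed* column reads "Retention of ≥ 80% of study participants for follow-up".
- **Retention formula (Data collection).** The only definition given is ("Number of patients who consent to participation) minus (number of patients who voluntarily withdraw) divided by (number of subjects who were randomised").

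**The concern.** The completeness measure says that it covers every outcome measure, but its list does not. It names two baseline items, REALM-R and demographics, and leaves out the knowledge questionnaire, which supplies two of the secondary outcomes. The team developed that questionnaire itself because no validated one existed, and it is the instrument on which the later trial would rest.

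The omission would matter less if the progression criteria covered the gap. For the 2-week score they do not. A form taken by telephone two weeks after surgery is not a day-of-surgery form, so the non-adherence row cannot count it. A patient who simply does not answer the call has not withdrawn, so the retention formula still counts that patient as retained.

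The pilot exists to show whether the definitive trial can be run. If delayed recall proves hard to collect, the two Table 1 rows that deal with data and follow-up could both read *Proceed* without showing it.

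**Working it through.** There is no stated figure to reproduce: the article makes no formal sample size calculation. The check is to count how much missing knowledge data each Table 1 row allows.

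**Inputs.** N = 40, 20 per group (Sample size). Non-adherence for *Proceed*: below 10% (Table 1). Retention bands: at least 80%, at least 60%, below 60% (Table 1). Retention = (consented − voluntarily withdrawn) / randomised (Data collection). Assumption: the 40 who consent are the 40 who are randomised.

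**Step 1: day-of-surgery knowledge form.** The post-intervention knowledge questionnaire is completed on the day of surgery, so on a plain reading it is one of the DOS questionnaires.
- Denominator all randomised: 3/40 = 7.5% passes and 4/40 = 10% does not. At most 3 may be incomplete, so at least 37/40 = 92.5% are complete.
- Denominator dHET arm only: 1/20 = 5% passes and 2/20 = 10% does not. At least 19/20 = 95% are complete, but control-arm forms are then not counted.

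This time point is therefore gated. Two points weaken the gate: Table 1 does not name the forms it means, and it gives no denominator.

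**Step 2: 2-week knowledge form, no withdrawals.** Let m be the number who miss the call. Retention as written is (40 − 0)/40 for every m. Completion is (40 − m)/40.

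| Missed calls m | Retention as written | Row reads | 2-week knowledge complete | Row if retention meant completion |
|---|---|---|---|---|
| 0 | 100% | Proceed | 40/40 = 100% | Proceed |
| 8 | 100% | Proceed | 32/40 = 80% | Proceed |
| 16 | 100% | Proceed | 24/40 = 60% | Proceed after changes |
| 20 | 100% | Proceed | 20/40 = 50% | Do not proceed unless problems overcome |
| 40 | 100% | Proceed | 0/40 = 0% | Do not proceed unless problems overcome |

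With all day-of-surgery forms complete, the non-adherence row reads 0/40 = 0% in each case, which is also *Proceed*.

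**Step 3: sensitivity to the no-withdrawal assumption.** The article does not say how many losses would be formal withdrawals. Suppose 16 patients lack the 2-week score and w of them withdrew:
- w = 0: 40/40 = 100%
- w = 8: 32/40 = 80%
- w = 16: 24/40 = 60%

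The row reads *Proceed* for any w up to 8. In all these cases only 24 patients have delayed recall data.

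**Step 4: comparison with the article's own planning.** Trial closure allows for up to 20% dropout: 0.20 × 40 = 8, leaving 32. Sample size gives 40% as an example of a dropout rate that would put a larger study in doubt: 0.40 × 40 = 16, leaving 24, the number it treats as its floor. The m = 16 case is the same proportionate loss on the 2-week score, and the written formula does not register it.

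**The case against.** A reader might infer that *Proceed* could be reached with the later trial's primary outcome largely missing, or that the decision rule is blind to knowledge data altogether. The documents do not support either. Table 1, not the completeness list, sets the progression criteria, and its day-of-surgery wording takes in the post-intervention knowledge form (Step 1). The Discussion does not say whether early or delayed recall would be primary, so the ungated score cannot be equated with that outcome. Two rows reading *Proceed* do not settle the decision either: recruitment and acceptability also count, and the article says the criteria will be considered, not applied automatically.

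The omission from the list may also be loose drafting. The governing words refer to every outcome measure, and the list mixes in baseline items, so it is hardly a careful closed list. Problems with the link to the knowledge quiz are recorded under Barriers. That softens the criticism of the list. However, Barriers has no row in Table 1.

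The strongest objection is that Table 1 speaks of retention for follow-up, and follow-up is the call that collects delayed recall. Read that way, *Proceed* already requires 32 of 40. That may well be what was intended, but the only formula given measures something else. The two places conflict and need to be reconciled. The direct remedy is in the retention definition, and the objection is right about that.

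It might also be said that unfinished dHET sessions and incomplete forms must be split into separate criteria. That is not needed: the and/or composite is stricter than either part alone. Separate reporting is enough.

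**Conclusion.** The point holds for the 2-week knowledge score. No stated criterion protects it. With no voluntary withdrawals, retention reads 100% while completion of delayed recall can lie anywhere from 100% to 0%. With 16 of 40 missing, the retention row reads *Proceed* as long as no more than 8 of the 16 formally withdrew. The omission from the completeness list is a separate and smaller inconsistency: the definition does not do what its own words say.

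The post-intervention score is protected on a plain reading, to at least 37 of 40, or 19 of 20 in the dHET arm. This rests on DOS questionnaires including the knowledge form, which Table 1 should state.

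The figures assume that all who consent are randomised. The split between silent non-response and formal withdrawal is not in the article, so a range is shown. The 40% non-response case is an illustration, not a forecast. The change should be made: the rule as stated can give a misleading reading, and correcting it needs no new data.

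**What to change.** 1. Add the knowledge questionnaire at baseline, post intervention and 2 weeks to the completeness list under Adherence to protocol.
2. State that DOS questionnaires in the Table 1 non-adherence row include the knowledge questionnaire, in both arms.
3. For the Table 1 retention row, define retention as the number randomised who complete the 2-week knowledge questionnaire divided by the number randomised. Keep the existing bands (at least 80%, 60% to below 80%, below 60%), so that *Proceed* needs at least 32 of 40 and the middle band at least 24 of 40.
4. Tabulate dHET non-completion (denominator: dHET arm) and incomplete forms (denominator: all randomised) separately. No new criterion is needed.

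The below-10% non-adherence band should not be carried over to the 2-week data. Losing the planned 8 of 40 (20%) would then satisfy retention but miss *Proceed* on completeness.

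The cost is wording and a few extra tabulations of data already collected. The downside is that reported retention may be less favourable, because unanswered calls will count.

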### Sample size

As this is a pilot study, a formal sample size calculation was not performed [36]. Sample sizes of between 24 (12 per group) and 50 have been recommended variously for pilot studies [37–40]. Following these broad recommendations, we chose a recruitment sample size of 40 (20 per group) which would allow for a moderate dropout rate. A significant dropout rate (e.g. 40%) would reduce the pilot sample size to below a minimum 24, in which case a planned larger study would be called into question in the first place, having possible external validity issues, pragmatic or ethical concerns.

### Interim analysis and stopping guidelines

As this is a pilot study run over a short time frame, we do not envisage a scenario where the trial will be ceased early.

### Randomisation

Sequence generation: generation of a random sequence will be performed using a computer-based programme by the trial statistician who will not have any contact with trial participants.Randomisation type: block randomisation (in blocks of two, four, six)Allocation concealment: assignments shall be enclosed in sequentially numbered, opaque, sealed envelopes and stored securely in a locked filing cabinet.Implementation: the trial statistician will generate the allocation sequence. They shall not have any direct contact with the study participants. Recruitment shall be carried out by the surgical team (consultant/research team). Upon confirmation of consent on the day of surgery, a numbered envelope containing randomisation data will be selected in sequence and the allocation assigned to the patient. The research assistant will be blind to the allocation sequence only. A unique study number will be assigned to each individual at the time of randomisation. All data collected will be input electronically into a database by the research assistant for analysis upon completion of the study.

### Blinding

By the nature of the intervention the participating patients will not be blinded. The responsible surgeon confirming consent prior to the procedure will be blind to participant allocation. The research assistant will be blind to the allocation sequence until opening of the sealed opaque envelope.

### Ethical approval and data protection

Ethical approval has been sought and received from both the Bon Secours Hospital and RCSI (202109017), on 14 May 2021 and 10 October 2021, respectively. All data will be pseudonymised (study number) and stored securely in a password-protected file in the Bon Secours Hospital systems for the duration of the study. Once analysis has been completed, data will be irrevocably anonymised by destroying the master key.

## Trial progression

### Continuation criteria

Continuation criteria (Table 1) will be considered to determine whether further evaluation of this intervention is warranted (to test the effectiveness of the intervention) [41, 42]. These criteria are primarily based around the primary objective of feasibility and the potential for effectiveness and system-wide implementation.

**Table 1 Tab1:** Continuation criteria VVEIN pilot study

	**Proceed to RCT**	**Proceed to RCT following some changes to the protocol**	**Do not proceed to RCT unless problems can be overcome**
Recruitment	Recruitment of ≥ 80% study participants within 4 months	Recruitment of ≥ 60% study participants within 4 months [41]	Recruitment of < 60% study participants within 4 months
Retention	Retention of ≥ 80% of study participants for follow-up	Retention of ≥ 60% of study participants for follow-up	Retention of < 60% of study participants for follow-up
Feasibility and acceptability	dHET intervention on day ward acceptable to > 75% of study personnel (score of 4 or 5 on Likert scale) and patients involved (score of 28 or above on CSQ-8)	dHET intervention on day ward acceptable to > 50–74% of study personnel (score of 4 or 5 on Likert scale) and patients involved (score of 28 or above on CSQ-8)	dHET intervention on day ward acceptable to < 50% of study personnel (score of 4 or 5 on Likert scale) and patients involved (score of 28 or above on CSQ-8)
Non-adherence	Non-adherence to the intervention in < 10% (dHET and/or DOS questionnaires incomplete)	Non-adherence to the intervention in > 11–20% (dHET and/or DOS questionnaires incomplete)	Non-adherence to the intervention in > 21% (dHET and/or DOS questionnaires incomplete)

*dHET* Digital Health Education Tool, *DOS* Day of surgery

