### Study setting

Patients who meet the inclusion criteria will be identified at the surgical outpatient department at the study location and invited to participate by a member of the research team. An initial consent and information process shall be carried out with patients deemed suitable for EVTA by their responsible surgeon. All patients (agreeable to participate and those unsure) will be provided with a PIL for the study approved by the local REC, for education purposes. Upon re-presentation to the day ward for their procedure, patients will be verbally reconsented for inclusion prior to randomisation and allocation to a study arm.

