### Trial closure

The trial shall be considered completed when a total of 40 participants have been randomised, as this will allow for up to 20% dropout rate.

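### The recruitment row of Table 1 does not say whether it counts patients who consent or patients randomised, and the protocol's outcome definition and its target of 40 point to different counts

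*Protocol article*

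**What the plan says.** Table 1, under Continuation criteria in the protocol article, grades recruitment at a 4-month mark. The best grade is "Recruitment of ≥ 80% study participants within 4 months", the middle grade starts at 60%, and the worst is "Recruitment of < 60% study participants within 4 months". The row does not state which event makes a patient recruited, or what the percentage is a share of.

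Three other places bear on how to read it:

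- **Data collection, primary outcomes.** The recruitment number is defined as a count of those who consent to take part. This is the only operational definition of the outcome.
- **Sample size.** "we chose a recruitment sample size of 40 (20 per group) which would allow for a moderate dropout rate". A figure split by group refers to randomised patients.
- **Trial closure.** "The trial shall be considered completed when a total of 40 participants have been randomised".

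Consent and randomisation are separate steps. Under Study setting, an initial consent and information process takes place in outpatients; on return to the day ward, "patients will be verbally reconsented for inclusion prior to randomisation". Under Randomisation, the envelope is selected only after consent has been confirmed on the day of surgery. Among the primary outcomes, the barriers item counts patients who are not randomised because of staffing, time or technology problems.

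**The concern.** Recruitment is a primary feasibility outcome and one of four rows that inform the decision on a definitive trial. The written outcome definition leads to a consent count and the target leads to a randomised count. Table 1 does not choose between them.

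What a definitive trial needs to know is the rate at which patients are randomised. A patient who agrees in clinic but is never randomised would count under one reading and not under the other. The same data could then fall in different columns, and the reading could be settled after the data are seen. No other row of Table 1 measures the loss between consent and randomisation.

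**Working it through.** **Inputs.** Target 40, 20 per group (Sample size, Trial closure). Thresholds 80% and 60% at 4 months (Table 1). Dropout allowed for 20% (Trial closure). Dropout called significant 40%, and minimum pilot size 24 (Sample size). The share of consenting patients who go on to be randomised is not given, so a range is assumed below.

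**The plan's own figures.** There is no power calculation to reproduce. The dropout arithmetic is 40 × (1 − 0.20) = 32 and 40 × (1 − 0.40) = 24. The second result equals the stated minimum of 24; the text says such dropout would go below it.

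**Thresholds with 40 as the base.** 0.80 × 40 = 32 and 0.60 × 40 = 24. The columns are therefore 32 or more, 24 to 31, and fewer than 24.

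**The same data under the two numerators.** Suppose 32 patients consent within 4 months.

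| Not randomised | Randomised | Grade if consents are counted | Grade if randomised are counted |
|---|---|---|---|
| 0 | 32 | 32/40 = 80%, Proceed | 80%, Proceed |
| 1 | 31 | 80%, Proceed | 31/40 = 77.5%, middle column |
| 8 | 24 | 80%, Proceed | 24/40 = 60%, middle column |
| 9 | 23 | 80%, Proceed | 23/40 = 57.5%, Do not proceed |

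At exactly 32 consents, one loss moves the grade by one column. A move of two columns needs 9 of 32 lost (9/32 = 28.1%).

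**Sensitivity to the assumed conversion.** Expected number randomised = 32 × conversion. The probability treats patients as independent (binomial with n = 32). Consents needed = 32 / conversion, rounded up.

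| Assumed conversion | Expected randomised of 32 | Probability of fewer than 24 randomised | Consents needed for 32 randomised |
|---|---|---|---|
| 95% | 30.4 | < 0.001 | 34 |
| 90% | 28.8 | 0.003 | 36 |
| 80% | 25.6 | 0.17 | 40 |
| 75% | 24.0 | 0.41 | 43 |
| 70% | 22.4 | 0.66 | 46 |

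**Would the retention row catch the loss?** Data collection defines retention as (consented − withdrawn) / randomised. With 32 consented, none withdrawn and 23 randomised, this is 32/23 = 139%. With 32 consented, 12 withdrawn and 24 randomised, it is 20/24 = 83%, still above the 80% threshold. Under that formula, patients who consent but are not randomised raise the rate.

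**The case against.** A reader might infer that Table 1 counts clinic consents, so that the trial can reach Proceed with too few patients randomised. The documents do not support that as a statement of fact, for four reasons.

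- Table 1 does not mention consent and does not refer back to the outcome definition. Sample size uses the word recruitment for the 40 split by group, and Trial closure counts 40 randomised. Read with those sections, the row means 32 of 40 randomised and the gap disappears.
- The outcome definition does not say that consent is counted in clinic. If it is counted when confirmed on the day of surgery, immediately before the envelope is selected, the consent and randomised counts nearly coincide. The barriers item also does not say that the patients it counts had already consented.
- The 4-month mark measures pace. Under Expected study duration, recruitment may run for up to 12 months, so a shortfall at 4 months is not a final shortfall. The criteria are to be considered, not applied mechanically.
- Eligible patients, consenting patients and patients not randomised (with reasons) are reported as separate outcomes, so losses before randomisation could be seen outside Table 1.

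All four points stand, and they limit the finding to an undefined term. They do not remove it. The only written definition of the outcome uses consent, the target uses randomisation, and the retention formula itself treats consented and randomised as different counts. The article prints the definition, the target and the thresholds, so this is not a detail left to a fuller document.

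**Conclusion.** The point holds as an ambiguity in a progression criterion. It does not show that the criterion counts the wrong patients. The recruitment outcome is defined by consent, the target of 40 by randomisation, and the Table 1 row fixes neither its numerator nor its base.

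If the consent definition is applied with 40 as the base, 32 consents grade as Proceed, whereas 31 randomised would be the middle column and 23 Do not proceed. This result rests on two assumptions: that 40 is the base, which is the natural reading, and that consent is counted before the day of surgery, which the documents leave open. The size of the effect cannot be stated, because no loss between consent and randomisation is given. A change of one column needs as little as one patient at the threshold. A change of two columns needs a loss of about 28%, which nothing in the documents predicts. The point is worth correcting because the row informs the go/no-go decision and the correction is cheap.

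**What to change.** In Table 1, define recruitment as the number of patients randomised within 4 months of the start of recruitment, divided by the target of 40. State the counts: 32 or more for Proceed, 24 to 31 for proceeding with some changes, and fewer than 24 for Do not proceed.

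Under Data collection, keep the number consenting as its own outcome, say at which step consent is counted, and report the conversion from consent to randomisation with the reasons for non-randomisation that are already to be collected. Align the retention formula at the same time, so that its numerator and denominator both refer to randomised patients and the rate cannot exceed 100%.

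The cost is wording in two places, with little or no new data collection. The downside is that the recruitment grade may look slightly less favourable than one based on consents.

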## Study methods

### Statement of design

The VVEIN study is a two-arm, randomised pilot feasibility trial to assess the practicality of supplementing the consent process for EVTA procedures with a dHET. This randomised feasibility study shall be carried out in accordance with the guidance set out by the Consolidated Standards of Reporting Trials (CONSORT) group for randomised pilot and feasibility trials. http://www.consort-statement.org [26]. The VVEIN study has been prospectively registered on ClinicalTrials.gov. (NCT Identifier: NCT05261412).

Participants shall be randomised in a 1:1 ratio to one of two parallel groups. Study flow is shown in Fig. 1. The dHET was co-designed with EIDO healthcare and contains information about EVTA procedures and the benefits, alternatives and risks of the procedure. EIDO healthcare information is delivered in a multimedia file with video animation, narration and graphics.

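### Two rows of the continuation table have bands that do not meet: 10% non-adherence and 50% or 75% acceptability have no column, and no rule covers staff and patients falling in different bands

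*Protocol article*

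**What the plan says.** The Continuation criteria section of the Protocol article says that Table 1 will be weighed in deciding whether a full trial is warranted. Its columns are: proceed, proceed after some protocol changes, and do not proceed unless problems can be overcome.

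- **Non-adherence.** First column: "Non-adherence to the intervention in < 10% (dHET and/or DOS questionnaires incomplete"; middle column: "Non-adherence to the intervention in > 11–20% (dHET and/or DOS questionnaires incomplete"; last column: above 21%.
- **Acceptability.** First column: above 75%; middle column: "dHET intervention on day ward acceptable to > 50–74% of study personnel"; last column: below 50%. Every cell names study personnel (4 or 5 on a Likert scale) and patients (CSQ-8 of 28 or more) under the same percentage band.
- **Recruitment and retention.** At least 80%, at least 60%, below 60%.

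On numbers, the Sample size section says "we chose a recruitment sample size of 40 (20 per group) which would allow for a moderate dropout rate", and the Trial closure section says of the 40 that "this will allow for up to 20% dropout rate".

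**The concern.** Read literally, non-adherence from 10% to 11% and from just above 20% to 21% belongs to no column. Neither does acceptability of exactly 50%, or from just above 74% to 75%. In a trial of this size percentages move in coarse steps, and some steps land exactly on these values.

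The acceptability row has a second difficulty. Personnel and patients are measured on different instruments, and no pooling is described. If all personnel but only 60% of patients find the tool acceptable, neither the first nor the middle column is met by both groups, and no tie-break is given.

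Feasibility is the primary objective, and Table 1 is the only progression rule in the article. Where it gives no column, the choice between neighbouring columns would be made after the data are known.

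**Working it through.** **Inputs.** 40 patients, 20 per group (Sample size); bands from Table 1. The article does not state the denominator for the non-adherence row, so both 20 and 40 are used. It gives no expected rates, so all true rates below are assumptions. The sample size follows general recommendations for pilots, not a formula. Its arithmetic is consistent: 40/2 = 20 per group, and 40 × (1 − 0.20) = 32 after the stated dropout.

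**Step 1: which counts have no column.** Every count x/n was placed in the literal bands.

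| n | Non-adherence | Acceptability |
|---|---|---|
| 20 | 2/20 = 10% | 10/20 = 50%, 15/20 = 75% |
| 40 | 4/40 = 10% | 20/40 = 50%, 30/40 = 75% |
| 39 | 4/39 = 10.3%, 8/39 = 20.5% | 29/39 = 74.4% |
| 32 | none | 16/32 = 50%, 24/32 = 75% |

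No count out of 20 or 40 falls between 20% and 21%. That gap needs another denominator, such as 39. Rounding to whole percentages does not rescue 10%, 50% or 75%, which are already whole.

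**Step 2: chance of landing in a gap.** P(X = x) = C(n,x) pˣ (1 − p)ⁿ⁻ˣ, summed over the gap counts.

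- Non-adherence, n=20, p=0.10: 190 × 0.10² × 0.90¹⁸ = 0.285.
- Acceptability, n=20, p=0.75: P(10) + P(15) = 0.010 + 0.202 = 0.212.

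**Step 3: at least one of the two rows unclassified.** With a and b the two gap probabilities and the rows independent, this is 1 − (1 − a)(1 − b). Results are from unrounded values.

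| True non-adherence / acceptability | n | a | b | At least one |
|---|---|---|---|---|
| 10% / 75% | 20 | 0.2852 | 0.2123 | 0.4369 |
| 10% / 75% | 40 | 0.2059 | 0.1448 | 0.3208 |
| 5% / 90% | 20 | 0.1887 | 0.0319 | 0.2146 |
| 5% / 90% | 40 | 0.0901 | 0.0036 | 0.0934 |
| 2% / 90% | 20 | 0.0528 | 0.0319 | 0.0831 |
| 2% / 90% | 40 | 0.0071 | 0.0036 | 0.0106 |

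These figures concern patients only and leave out any staff/patient mismatch.

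**Step 4: staff and patients in different bands.** The article does not say how many personnel will rate the tool; only two surgeons are counted. Assuming 3 to 10 raters, 20 patients, and staff and patients independent, the acceptability row has no column (gap or mismatch) in 62–87% of trials if both true rates are 75%, but in 9–37% if both are 90%. That spread is too wide for a headline figure. It shows only that the missing rule can matter.

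**Step 5: does the repair work?** With acceptability ≥75% / 50 to <75% / <50% and non-adherence ≤10% / >10–20% / >20%, every count out of 20 or 40 has exactly one column. Out of 20, the bands are ≥15 / 10–14 / ≤9 and ≤2 / 3–4 / ≥5.

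**The case against.** The strongest reply is that this is careless notation in a table meant to guide judgement. Each gap lies between adjacent columns, so no result is left hanging between an outright go and an outright stop, and the last column is itself conditional. The criteria are to be considered, not applied mechanically. This stands, and it limits the severity. It does not tell the investigators which column 2/20 or 15/20 belongs to.

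A reader might infer that an unclassified result is the likely outcome, citing 44%. The documents do not support that. The figure needs both true rates to sit on their cut-offs at once, and the article gives no expected rates. Independence is also doubtful: the CSQ-8 is a day-of-surgery questionnaire, so a non-adherent patient may also be missing from the acceptability denominator. In the extreme case where every non-adherent patient lacks a CSQ-8, 44% becomes 33%.

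The acceptability cells could instead be read hierarchically, so that failing the first column in either group drops the row to the next. The upper limit of 74% in the middle cell counts against this, because personnel at 100% do not satisfy it. Pooling the two groups would remove the mismatch, but none is described, and the gaps would remain.

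A reader might also extend the fault to recruitment and retention. Those rows have no gap. Their middle band overlaps the first, but they read clearly from left to right.

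**Conclusion.** The point holds for the acceptability and non-adherence rows only. Their bands do not meet, and 10% non-adherence and 50% or 75% patient acceptability, all attainable with 20 or 40 patients, have no column. The gap above 20% to 21% arises only at other denominators.

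The chance of at least one unclassified row runs from about 44% (n=20) or 32% (n=40) with true rates on the cut-offs to about 8% or 1% at 2% non-adherence and 90% acceptability. It is about 21% or 9% at 5% and 90%. These figures rest on assumed rates and independent rows, and they do not show that an unclassified result is likely.

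The missing rule for staff and patients in different bands follows from the literal cells; its size cannot be fixed without the number of raters. This should be fixed. It does not undermine the design, since the affected results fall between neighbouring columns of a table that informs judgement.

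**What to change.** Before results are seen:

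- Make the bands of the two rows contiguous, so that every value has exactly one column. The bands tested in the working are one example; which side owns each boundary is the sponsor's choice.
- State the denominator for each row (dHET patients or all randomised; with or without missing questionnaires), and preferably give the bands as counts too.
- Classify personnel and patients separately and let the worse band set the acceptability row.

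Recruitment and retention need no change. Writing their middle band as 60 to <80% would be optional tidying.

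The cost is an edit to one table. It needs no extra data, patients or procedures.
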